### Ethics and regulatory approval

The Newcastle upon Tyne Hospitals NHS Foundation Trust (NuTH) is the sponsor for the entire study. NuTH is responsible for ensuring appropriate regulatory and ethical approvals are in place at all participating sites. Ethical approval was issued for all sites by: Ethical Commission (EC) of the Medical Faculty of Friedrich-Alexander University Erlangen-Nürnberg (Erlangen-Nürnberg, vote 535_20 B); EC of the Medical Association of Schleswig-Holstein (Grosshansorf; vote 023/21 I); EC of the Medical Faculty of Christian-Albrechts-University Kiel (Kiel; vote D 630/20); EC Research of University Hospitals Leuven (vote S64977); EC dell’Insubria (Milan; vote 196 del 2021); Committee of the Protection of Persons, South-Mediterranean II (Montpellier; vote 221 B08); EC of the Medical Faculty of Eberhard-Karls-University Tübingen (Stuttgart; vote 976/2020BO2); Helsinki Committee of the Tel Aviv Sourasky Medical Center (Tel Aviv, vote 0551-19-TLV 2020); Regional Committee for Medical and Health Professional Research Ethics (Trondheim; vote 216069); London-Bloomsbury Research Ethics Committee (all UK sites; vote 20/PR/0792); Cantonal EC Zürich (Zurich; vote 2021–00601); EC of Medical Research at Barcelona Hospital Clinic (Barcelona site 1; vote HCB/2021/0445), EC of Medical Research at Parc del Salud (Barcelona site 2; vote 2021/9797/I); EC of Research at University Hospital Germans Trias i Pujol (Barcelona site 3; vote PI-21-093); EC of Research at Viladecans Hospital (Barcelona site 4; vote PR129/21); Sotiria Hospital Scientific Board (Athens; vote 1560/18-1-21). A Site Agreement between the sponsor and each site is required. Sites must not start recruitment until the sponsor has issued the regulatory Green Light for them to do so. This involves confirmation that the site has appropriate staffing, resources and documentation in place to undertake the study. The sponsor is also responsible for approving all study amendments, and for reviewing protocol deviations and Serious Adverse Events.

#### Study registration

The study was registered at the ISRCTN registry on 12/10/2020 titled Clinical validation of a mobility monitor to measure and predict health outcomes (ISRCTN Number: 12051706).

### Outcome measures

In order to meet the objectives of the CVS, digital mobility outcome measures as well as general and disease specific outcome measures (constructs) will be assessed.

#### Digital mobility measures

Daily-living mobility performance and capacity will be assessed directly using wearable sensor devices. First, participants will wear the McRoberts MoveTest (McRoberts B.V., The Hague, The Netherlands) to ‘instrument’ and objectively quantify physical assessments. Following the agnostic device approach proposed in the technical validation study [36], two different but metrologically equivalent devices will be adopted for the daily living monitoring. Accordingly, either the McRoberts MoveMonitor+ or the Axivity AX6 (Axivity Ltd, Newcastle Upon Tyne, UK) will be used to record free-living activity data over a period of at least seven consecutive days in an unsupervised condition after completion of the on-site assessment. Patients will be followed up using the same device at each time point. The MoveMonitor+ will be worn in a belt that is secured around the waist of the patients, while the AX6 will be directly secured to the skin using an adhesive fixation method. Mobilise-D walking-related DMOs include, among others, real world walking speed, quantitative measures of the total number of walking bouts, the percent of time spent walking which reflects the total walking in relation to the overall walking and non-walking activity, stride/step duration, median walking bout duration, median number of steps, and median cadence per bout. Quality-related sensor-derived measures include frequency-derived measures that reflect variability of the gait pattern such as swing and stance phase duration, variability and asymmetry of step time, stride time, swing time, stance time and velocity stride length which quantity gait rhythmicity and consistency [36]. This further aligns with the categories of DMOs identified recently which are pace, volume, rhythm, phases, variability, base of support and asymmetry of gait [35].

#### Clinically relevant outcome measures (constructs)

A wide range of core and cohort specific outcome measures will be collected, spanning patient-reported outcomes (PRO), observer-reported outcomes (ObsRO), clinician-reported outcomes (ClinRO), performance-based outcome physical measures (PerfO-P), and performance-based outcome cognitive/mental measures (PerfO-C). The assessments will be completed according to the assessment schedule (Fig 1), with all outcome measures detailed in Table 2.

**Table 2 pone.0269615.t002:** Cohort specific sample size calculation.

Cohort	Hypothesis	Critical value	Time frame	Assumptions	Loss to follow-up	Statistical method proposed	Sample size
Parkinson’s Disease	Reduced gait speed is associated with increased fall risk	a coefficient of 1 for a 1 m/s decline in walking speed	24 months [57]	(i) a standard deviation of real‐world walking speed of 0.11 m/s or higher [58, 59], (ii) a 2‐y rate of falls of 1.6 or higher [59]	20%	Poisson regression model	600
Multiple Sclerosis	Reduced RWS is associated with fall frequency	a coefficient of >0.5 for a 1 m/s decline in walking speed	24 months	(i) a standard deviation of real‐world walking speed of 0.13 m/s or higher (19), (ii) a 2‐y rate of falls of 5 or higher [60, 61]	10%	Poisson regression model	600
Chronic Obstructive Pulmonary Disease	RWS is associated with COPD exacerbations	an odds ratio of 1.43 for a 0.1 m/s decline in walking speed [62]	12 months	(i) a standard deviation of real‐world walking speed of 0.115 or higher [55]l, (ii) a proportion of exacerbations up to 0.6 [24, 62, 63]	30% [24, 62, 63]	Logistic regression model	600
Proximal Femoral Fracture	RWS is associated with care home admission	odds ratio of 2.55 in the risk of admission on slow RWS vs normal/high RWS [64]	6 months	(i) a ratio of low RWS vs normal/high RWS of 1:2, (ii) a six month proportion of admissions to care home of 10 to 30% [46, 65]	30% [46, 65]	Logistic regression model	572 (≈600)

RWS, real world walking speed.

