#### Primary outcome measures (Global and cohort-specific)

There is one global primary outcome measure and four cohort specific primary outcome measures. The Late-Life Function and Disability Instrument (LLFDI) [42, 43] represents the core primary outcome measure. The LLFDI was developed as a comprehensive questionnaire assessing function and disability for use in community-dwelling older adults. It contains items that represent functional limitations in performing discrete physical tasks encountered in daily routines and disability related to participation in major life tasks and social roles within a typical sociocultural and physical environment. The LLFDI assesses function in 32 physical activities in three dimensions (upper extremity, basic lower extremity, and advanced lower extremity) and disability in 16 major life tasks.

The cohort specific primary outcome measures are fall frequency during 24-month follow-up in the PD and MS cohorts, occurrence of moderate to severe COPD exacerbations during the first 12-months follow-up in the COPD cohort and admission to a care home at six-months follow-up within the PFF cohort.

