### Statistical analysis

#### Sample size

Sample size was calculated separately for each cohort according to its main disease-specific primary outcome, as well as with 24-months changes in LLFDI score as global primary outcome. The estimated sample size aiming for a sample that allowed the disease-specific objectives as well as the global objectives to be met.

*Cohort specific sample size calculations*. Sample size calculation for each disease cohort showed that 600 participants will be required in each cohort in order to achieve a statistically significant outcome of the respective hypothesis critical value with a power of 90% and an alpha error of 0.05. Details of the hypotheses and the assumption underpinning these calculations are summarised in Table 2.

*Global sample size calculations*. Sample size calculation for the global primary outcome is based on the hypothesis that baseline real-world walking speed is associated with changes in LLFDI score (0–100) within 24 months. Using (i) a minimal detectable change of 95% confidence of 3.41 in LLFDI functional component [53] representing a clinically relevant intervention effect [54], (ii) a standard deviation of the mean change in LLFDI functional component of 30.1 points [41], (iii) a standard deviation of 0.29 m/s for real-world walking speed [55], (iv) a clinically relevant and measurable difference of 0.1 m/s in real-world walking speed between two patients [56], and (v) based on a linear regression analysis a sample size of 67 subjects would allow identifying a statistically significant change, with a power of 80% and an alpha error of 0.05. Including an expected drop-out rate of 10–30% the final sample size would be n = 81. The available sample size of 2,400 patients, derived from the sum of sample sizes required for the evaluation of the abovementioned cohort-specific outcomes provides sufficient power to test the general LLFDI hypothesis.

The proposed statistical method will be amended upon data completion and prior analysis should the data distribution require a more appropriate methodology.

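### PFF sample size: the stated 90% power needs at least about 15% of the cohort admitted; at the row's own lower bound of 10%, power is about 79% (572 enrolled) or 81% (600)

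*Protocol article*

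**What the plan says.** The PFF cohort-specific primary outcome is "admission to a care home at six-months follow-up within the PFF cohort" (Primary outcome measures). The PFF row of Table 2 sets out the sample size inputs:

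- effect: "odds ratio of 2.55 in the risk of admission on slow RWS vs normal/high RWS"
- exposure split: "a ratio of low RWS vs normal/high RWS of 1:2"
- event proportion: "a six month proportion of admissions to care home of 10 to 30" per cent
- loss to follow-up: 30%
- method: "Logistic regression model"
- result: 572, rounded to about 600

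The Sample size section says that 600 participants in each cohort meet the Table 2 hypotheses "with a power of 90% and an alpha error of 0.05". It makes no exception for any cohort and does not say whether alpha is one- or two-sided. Neither place says which value between 10% and 30% produced 572, or whether the range describes the whole cohort or one speed group.

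**The concern.** For a fixed odds ratio and a fixed split, the required number depends strongly on how common the event is. A single sample size cannot give 90% power at every point of a threefold range of event proportions. It can give at least 90% throughout only if it was computed at the least favourable end, which here is 10%. The PD and MS rows of the same table state their event-rate and standard-deviation assumptions as a given value or higher, so there the stated value is the floor at which the claim is meant to hold. Read the same way, the PFF floor is 10%.

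At stake is the power statement for the PFF cohort's own primary hypothesis. If it fails at the lower bound, a null result at a low admission proportion would be read against a type II error of 10% when the real figure is about 20%.

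**Working it through.** **Inputs.** From Table 2: OR = 2.55; one third slow, two thirds normal/high; admission proportion P from 10% to 30%; 30% loss; 572 or 600 enrolled. From Sample size: power 90%, alpha 0.05. Assumptions: alpha is two-sided; P is the proportion in the whole cohort; no covariate adjustment.

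**Evaluable numbers.** 572 × 0.7 = 400; 600 × 0.7 = 420.

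**Step 1: group risks.** Let p0 be the risk in the normal/high group and p1 the risk in the slow group. Solve

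p1/(1 − p1) = 2.55 × p0/(1 − p0) and (1/3)p1 + (2/3)p0 = P.

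- P = 10%: p0 = 6.97%, p1 = 16.05%
- P = 15%: p0 = 10.75%, p1 = 23.5%
- P = 30%: p0 = 23.2%, p1 = 43.6%

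**Step 2: required size.** For two proportions at 1:2, the slow-group size is

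n1 = [1.960 × √(1.5·P(1 − P)) + 1.282 × √(p1(1 − p1) + p0(1 − p0)/2)]² / (p1 − p0)²,

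with N = 3·n1 evaluable and N/0.7 enrolled.

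*Reproducing the plan's figure.* At P = 15%, N = 398 evaluable and 398/0.7 = 569 enrolled, against the stated 572. Solving for 572 exactly gives P = 14.9%. So 572 can be reproduced, but at a proportion the row does not state.

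*At the lower bound.* At P = 10%, n1 = (0.7201 + 0.5240)² / 0.09076² = 187.9. This gives N = 564 evaluable and about 805 enrolled.

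*At the upper bound.* At P = 30%, N = 246 evaluable and 352 enrolled.

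**Step 3: power at the planned size.** Power = Φ{[(p1 − p0)√n1 − 1.960·√(1.5·P(1 − P))] / √(p1(1 − p1) + p0(1 − p0)/2)}.

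For P = 10% and 400 evaluable (n1 = 133.3): (1.0480 − 0.7201)/0.4089 = 0.802, so power = 78.9%.

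| Overall admission | 572 enrolled (400) | 600 enrolled (420) |
|---|---|---|
| 10% | 78.9% | 80.7% |
| 12% | 84.5% | 86.1% |
| 14% | 88.5% | 89.9% |
| 15% | 90.1% | 91.4% |
| 20% | 95.1% | 95.9% |
| 30% | 98.4% | 98.8% |

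The 90% threshold is at 14.9% for 572 and 14.1% for 600.

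**Cross-checks at 10%.** The Wald test on the log odds ratio gives 79.4% (572) and 81.3% (600). A simulated likelihood ratio test gives 79.0% and 80.2%. A one-sided alpha does not rescue the claim: 665 enrolled would still be needed.

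**Alternative reading.** Take 10% as the risk in the normal/high group. Then p1 = 22.1%, and the overall proportion is (22.1 + 2 × 10)/3 = 14.0%. The requirement is 421 evaluable, about 601 enrolled. Power is 88.6% at 572 (Wald 89.4%) and 89.9% at 600 (Wald 90.7%).

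**The case against.** The best defence is that the range may describe the normal/high group. On that reading the 600 to be enrolled delivers 90% at the lower bound to within rounding, and more above it. This stands as a possibility, because the row names no group. It is not the plain meaning of a six-month proportion of admissions, and if it is what was meant, the row has to say so.

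A second defence is that even on the whole-cohort reading, power is at or above 90% over about three quarters of the range and is still near 80% at the worst point. That is correct and limits the severity. It does not make an unqualified 90% true at 10%.

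A third is that the analysis will probably use speed as a continuous variable. The PFF hypothesis is worded for walking speed as such, and the Analysis plan models baseline levels of the digital outcomes and checks non-linearity with generalised additive models. Continuous speed could recover power: if speed is normally distributed, a split at the lower third keeps about 59.5% of the information, and 564 × 0.595 = 336, below the 400 available. This too is fair. However, the row's power is stated for a slow versus normal/high odds ratio, and the document gives no effect per m/s for this cohort from which to restate it.

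Several stronger readings are tempting and not supported:

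- *That 572 was computed at 15%.* The match is close, but 572 is also near the uninflated need at 10% (564), which would mean that the 30% loss was not added. The document does not settle which.
- *That 10% is the likelier value*, because care home residents are excluded and enrolment runs to 52 weeks after surgery. The protocol gives no figure for this. Existing residents cannot be newly admitted, so leaving them out could raise the proportion.
- *That the analysis will dichotomise speed.* Nothing in the Analysis plan says so.

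**Conclusion.** The point holds, at moderate severity. On the plain whole-cohort reading, with two-sided alpha 0.05 and the row's own odds ratio, split and loss, the 90% claim is met from about 15% admitted (about 14% with 600 enrolled) up to 30%. It is not met in roughly the lowest quarter of the stated range with 572 enrolled, (14.9 − 10)/20, or the lowest fifth with 600, (14.1 − 10)/20. The type II error at the lower bound is about 21% or 19%, against the promised 10%. The size of the shortfall rests on the whole-cohort reading; on the normal/high-group reading it is about one percentage point or less. On either reading the row leaves out what a reader needs to check the claim.

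**What to change.** In the PFF row of Table 2, state which admission proportion, and in which group, 572 rests on. If the range is the whole-cohort proportion, restate the result as: 572 enrolled (400 evaluable) gives about 79% power at 10% admitted, 90% at 15% and 98% at 30%; 600 enrolled (420 evaluable) gives about 81%, 91% and 99%. If 10% is the normal/high-group risk, label it so and give about 89% (572) and 90% (600) at that value. State that alpha is two-sided. In the Sample size section, qualify the general 90% claim for the PFF cohort accordingly.

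The cost is wording in one table row and one sentence. No design, outcome or data collection changes. The price is a less favourable stated power at the low end of the range.

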#### Primary outcome measures (Global and cohort-specific)

There is one global primary outcome measure and four cohort specific primary outcome measures. The Late-Life Function and Disability Instrument (LLFDI) [42, 43] represents the core primary outcome measure. The LLFDI was developed as a comprehensive questionnaire assessing function and disability for use in community-dwelling older adults. It contains items that represent functional limitations in performing discrete physical tasks encountered in daily routines and disability related to participation in major life tasks and social roles within a typical sociocultural and physical environment. The LLFDI assesses function in 32 physical activities in three dimensions (upper extremity, basic lower extremity, and advanced lower extremity) and disability in 16 major life tasks.

The cohort specific primary outcome measures are fall frequency during 24-month follow-up in the PD and MS cohorts, occurrence of moderate to severe COPD exacerbations during the first 12-months follow-up in the COPD cohort and admission to a care home at six-months follow-up within the PFF cohort.

#### Secondary outcome measures

Secondary outcome measures encompass sociodemographic (descriptive data) and clinical outcome measures including physical measures, mobility performance, and neuropsychological measures to describe how participants feel, function, or survive (Table 2).

Primary and secondary outcomes will be used as the constructs against which the DMO’s predictive ability, construct validity, estimates of the Minimum Important Difference, and ability to detect change over 24 months will be assessed. Table 2 includes details of all assessments and outcome and their respective validation use.

The secondary outcome measures of special interest for each cohort are as follows:

The Movement Disorder Society Unified Parkinson’s Disease Rating Scale (MDS-UPDRS) [44] will be used to assess predictive capacity, construct validity, detect change over 24 months as well as determine the MID amongst the PD cohort. The MDS-UPDRS describes disease progression, and it is separated into four different domains including cognitive function, behaviour and mood, activities of daily living (ADL), and motor examination.

The Expanded Disability Status Scale (EDSS) [45] will be used to assess predictive capacity, construct validity, detect change over 24 months as well as determine the MID amongst in the MS cohort. The EDSS is an ordinal clinical rating scale to quantify disability in MS ranging from normal neurologic examination (0) to death due to MS (10).

Forced expiratory volume in one second (expressed as a percentage of predicted norm) (FEV-1) will be used to assess predictive capacity, construct validity, detect change over 24 months as well as determine the MID amongst for the COPD cohort. The spirometry test measuring FEV-1 is used to diagnose and stage COPD.

The Short Physical Performance Battery (SPPB) [46] will be used to assess predictive capacity, construct validity, detect change over 24 months as well as determine the MID amongst the PFF cohort. The SPPB assesses lower extremity function and mobility, consisting of a static balance task, a five-repetition chair-rise test, and a 4-meter walk test. Further assessments include the Pain Visual Analogue Scale [47], the Euro-QoL 5D5L [48], the Timed Up-and-Go test [49], the Short Falls Efficacy Scale–International [50], the UCLA Loneliness and Social Isolation Scale [51], and the Montreal Cognitive Assessment [52] (see Table 2).

#### Diaries

MS and PD participants will be asked to complete a falls diary and return these on a monthly basis recording the relevant events (exacerbation, change of medication, falls) as and if they occur during each month. COPD participants will be asked to complete exacerbation diaries including medication change, hospitalisation, unplanned doctor’s visits, and falls and return diaries at subsequent study visits. Other measures.

### Environmental factors

Given the fact that the CVS will not be carried out under controlled laboratory settings, meteorological variables (such as daily maximum temperature, precipitation, snowfall, and mean wind speed, among others) will be collected to characterise the participants’ weather condition exposure and assess the effect of these environmental factors on the digital mobility outcomes.

### Patient and Public Involvement and Engagement (PPIE)

Prior to the design of the CVS, patients’ opinions regarding acceptability of wearable devices to measure gait and physical activity were collected and explored. Patients were involved in the design of the study protocol, including the consideration of COVID-19 protocols and risks, and in the review of patient-facing documents to ensure readability and understanding. Throughout the CVS, a dedicated Patient and Public Advisory Group (PPAG) will advise on key topics such as the identification of meaningful mobility outcomes and patient needs and concerns regarding digital technology. Furthermore, the PPAG will co-design and comment on research plans, protocols and materials, and assist in the interpretation of results and their dissemination.

### Management, safety monitoring, and steering committee

Formal oversight of the Mobilise-D CVS will be undertaken by the Study Management Group (SMG) and the independent clinical Study Steering Committee (SSC). Informal oversight of the Mobilise-D CVS will be undertaken by the Assessor Support Group (ASG). All committees will run for the study duration.

### Study management group

The SMG will be responsible for the day-to-day management of the study. The group includes the key individuals responsible for undertaking the study. The SMG will monitor the study progress, ensure protocol adherence, and take appropriate action to safeguard participants and the quality of the study. Data issues and safety will be a priority for the SMG. This is a low risk observational study that does not require a specific Data Monitoring Committee.

### Study steering committee

The SSC will provide overall supervision of the study. The SSC has an independent chair and majority independent representation including patient representatives. The SSC will monitor the study progress and is responsible for making top-level decisions. The SSC carries the responsibility for deciding whether the study should be stopped on grounds of safety or efficacy.

### Assessor support group

The ASG will be responsible for the day-to-day running of the study and to provide general support to study assessors. The ASG is managed by the study coordinators. Individual cohort leads are responsible for providing cohort specific oversight and support.

